### Interim analysis {21b}

There is no planned interim analysis.

### Methods for additional analysis {20b}

An interaction analysis to test the effect of the intervention delivery mode (on-site or remote) is planned.

### Methods in analysis to handle protocol non-adherence and any statistical methods to handle missing data {20c}

The value 0 (zero) will be imputed to replace the missing data in the analysis that will follow the intention-to-treat principle.

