#### Secondary outcomes

The secondary outcomes are divided in health behaviors (health literacy [39], physical activity level [40], exercise self-efficacy [41], adherence to Mediterranean diet [42], and medication adherence [43]) and cardiometabolic health parameters (glycemic control [44], anthropometric characteristics, and cardiac autonomic control [45]), as described in Table 2.

**Table 2 Tab2:** Description of the secondary outcomes

Secondary outcomes	Measurement tools	Measurement description/range
Health literacy	NVS health literacy instrument	Total score ranging from 0 (no health literacy) to 6 (highest health literacy)
Physical activity level	Steps	Total steps/week and average of steps/day obtained from daily steps number for seven days measured by a pedometer
Exercise self-efficacy	Brazilian Portuguese version of BESES	Total score ranging from 0 (not confident) to 100 (completely confident)
Adherence to Mediterranean diet	Brazilian Portuguese version of the MDS	Total score ranging from 0 (no adherence) to 13 (highest adherence to Mediterranean food pattern)
Medication adherence	Brazilian version of the MAT ADOs and MAT insulin	Total score ranging from 0 (no adherence) to 7 (highest medication adherence)
Glycemic control	Results from A1c exams	Routine laboratory tests dated no longer than 3 months before the study assessment point
Anthropometric characteristics	BMI and waist circumference	Weight (kg) and height (m) measured to calculate BMI (kg/m^2^), waist circumference (cm) measured at the superior border of the iliac crest
Cardiac autonomic control	Five-minute resting HRV	SDNN (ms), RMSSD (ms), pNN50 (%), SD1 (ms), SD2 (ms), SD1/SD2 ratio, LF (ms^2^), HF (ms^2^), LF (nu), HF (nu), LF/HF ratio, TP (ms^2^)

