#### Tertiary outcomes

The tertiary outcomes included in this study will be program adherence, satisfaction with the program, diabetes-related morbidity, quality of life, depression, and diet quality.Program adherence will be measured by the attendance rate in the program for each participant. The attendance rate of participants in the on-site delivery mode will be calculated based on the number of education classes and/or exercise sessions attended, divided by the total number of education classes and/or exercise sessions offered. For participants in the remote delivery mode, the attendance rate will be determined by the number of weeks exercise and /or study diaries were filled out, divided by the program’s duration in weeks.Satisfaction with the program will be measured by questionnaires developed by the researchers. For participants in the on-site delivery mode, the level of satisfaction with the patient education program will be assessed by an 11-item questionnaire, and with the exercise program by a 4-item questionnaire. For participants in the remote delivery mode, the level of satisfaction with the patient education program will be assessed by a ten-item questionnaire and with the exercise program by a five-item questionnaire.Diabetes-related morbidity will be assessed through the number and description of acute complications and diagnoses of chronic complications of diabetes, along with the number of hospitalizations associated with diabetes. The information will be collected using a three-item tool during the 6-month follow-up period.Quality of life will be evaluated using the Medical Outcomes Study 36-Item Short-Form Health Survey (SF-36) [46]. The total scores range from 0 (indicating no quality of life) to 100 (indicating the highest quality of life). This is obtained through a 36-item tool distributed across various physical and mental health domains, including physical functioning, social functioning, role–physical, bodily pain, mental health, role–emotional, vitality, and general health.Depression will be measured by the Brazilian version of the Center for Epidemiological Scale—Depression (CESD) [47]. The total score ranges from 0 (indicating no depressive symptoms) to 60 (indicating the highest level of depressive symptoms). This is obtained through a 20-item tool used to rate how often the interviewed experienced symptoms associated with depression over the past week, such as restless sleep, poor appetite, and feeling lonely. Response options range from 0 to 3 for each item (0 = rarely or none of the time, 1 = some or little of the time, 2 = moderately or much of the time, 3 = most or almost all the time).Diet quality will be measured through the consumption of macro and micronutrients. Food consumption will be assessed using an adapted version of a validated Food Frequency Questionnaire (FFQ) for Brazilian individuals with type 2 diabetes [48, 49], evaluating consumption frequency (daily, weekly, monthly, or yearly), number of portions, and serving size (small, medium, large or extra large). The adaptation of the FFQ was necessary since the individuals in this research have different eating habits than in the validated FFQ study, so regional adaptations were necessary. This adaptation was made based on a food diary on three non-consecutive days, including a weekend day carried out with 65 volunteers with type 1 or type 2 diabetes [42]. The final FFQ consists of 104 food items distributed across eight food groups (“cereals, tubers, roots, and derivatives”; “vegetables and legumes”; “fruits”; “beans”; “meat and eggs”; “milk and dairy products”; “oils and fats”; “sugars and sweets”), as well as 11 items investigating beverages, 4 items investigating oilseeds, and 1 item investigating food supplement.

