### Sample size {14}

The sample size was calculated considering the ISWT distance as the primary outcome, using parameters derived from a previous study involving educational intervention in cardiac rehabilitation [50]. The calculation was performed using R Software version 3.4.3, with the following parameters: a moderate effect size (*d* = 0.20), 80% statistical power, a 5% alpha level, one-sided test, two arms, and three measurements. A total sample size of 200 participants (100 per arm) was determined. Assuming a 20% attrition rate, based on a previous study [50], 120 participants would be enrolled in each arm to ensure that 200 participants complete the study protocol.

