#### Primary and secondary outcomes

Primary and secondary outcomes will be presented as central tendency and dispersion measures. Data distribution will be analyzed using the Shapiro–Wilk test. The analysis of variance (2 × 2 ANOVA) will compare data between baseline and post-intervention and between groups. An alpha of 5% will be considered for statistical significance, and post hoc comparisons will be performed to detect two-by-two differences. In case of missing data, the statistical procedures will follow the intention to treat.

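### Replacing every missing value with 0 puts worst-case, best-case or impossible values into the analysis: it dilutes real effects and, if dropout differs between arms, biases the comparison

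*Protocol article*

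**What the plan says.** Item 20c of the Protocol article gives one missing-data rule: "The value 0 (zero) will be imputed to replace the missing data in the analysis that will follow the intention-to-treat principle". It is not restricted to any outcome or visit. The statistical methods for primary and secondary outcomes add only this: "In case of missing data, the statistical procedures will follow the intention to treat". No other method and no sensitivity analysis is named. The same section sets the analysis: "The analysis of variance (2 × 2 ANOVA) will compare data between baseline and post-intervention and between groups". Quality of life, depression and diet quality are to be analysed in the same way.

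The outcome sections define what 0 means:

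- **ISWT (primary):** distance in metres, so 0 is no distance walked.
- **DATE-Q (primary):** 0 to 20, and 0 is no knowledge.
- **Health literacy, exercise self-efficacy, Mediterranean diet, SF-36:** 0 is the worst score.
- **Medication adherence:** "Total score ranging from 0 (no adherence) to 7 (highest medication adherence".
- **Depression (CESD):** "The total score ranges from 0 (indicating no depressive symptoms) to 60", so 0 is the best score.
- **A1c, BMI, waist circumference, most HRV measures:** 0 cannot occur.

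On how much will be missing, the sample size section says: "Assuming a 20% attrition rate, based on a previous study". It plans to enrol 120 per arm.

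**The concern.** Intention to treat means analysing participants in the arm to which they were randomised. It does not supply a value for an outcome that was not observed, and 0 is not a neutral choice here. A participant who misses the post-intervention visit becomes the worst case on both primary outcomes, the best case on depression, and an impossible case on A1c.

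Two consequences follow. Even with equal dropout, the zeros shrink a true difference and add a large artificial spread. With unequal dropout, the difference in dropout itself becomes a treatment difference: it counts against the arm with more dropout on ISWT and DATE-Q, and in its favour on A1c, BMI, waist circumference and CESD. Unequal dropout is plausible, because participants know their allocation and one arm has 18 additional classes.

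**Working it through.** **Share of imputed values.** 20% of 120 is 24 per arm, leaving 96. If all attrition fell before the post-intervention visit, 20% of post-intervention values would be zeros. That is 10% of all values in the baseline and post-intervention ANOVA. Attrition in the plan runs to the end of the 6-month follow-up, so the share at 12 weeks may be lower.

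**Inputs not in the document (assumed).** ISWT mean μ = 400 m, SD σ = 120 m, baseline to post-intervention correlation ρ = 0.7, true effect 0.40 SD = 48 m, 120 per arm, values missing completely at random, zeros on the raw post-intervention value, two-sided test at the plan's 5% level.

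**Formulas.** If a fraction p of post-intervention values is set to 0:

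- mean = (1−p)μ
- variance of the post value = (1−p)σ² + p(1−p)μ²
- variance of the change from baseline = that variance + σ² − 2(1−p)ρσ²

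The group-by-time test in a 2 × 2 design is the two-sample test on the change.

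**Equal missingness, 20% per arm, true effect 48 m.**

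- Difference: 0.8 × 448 − 0.8 × 400 = 38.4 m.
- Post-value variance, Ex: 0.8 × 14,400 + 0.16 × 400² = 37,120 (SD 193 m). ExLE: 11,520 + 0.16 × 448² = 43,633 (SD 209 m).
- Change variance: add 14,400 and subtract 2 × 0.8 × 0.7 × 14,400 = 16,128. This gives 35,392 and 41,905.
- Standard error: √((35,392 + 41,905)/120) = 25.4 m. Ratio 38.4/25.4 = 1.51, so power is about 33%. Simulation of the same test gives 33–34%.
- Observed cases, 96 per arm: change variance 2 × 14,400 × 0.3 = 8,640, standard error √(2 × 8,640/96) = 13.4 m, ratio 48/13.4 = 3.58, power about 95%.

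**Same calculation at the plan's stated effect size** ("a moderate effect size (*d* = 0.20", here 24 m). Zeros: difference 0.8 × 24 = 19.2 m; change variances 35,392 and 38,556; standard error 24.8 m; power about 12%. Observed cases: 24/13.4 = 1.79, power about 43%.

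**Same calculation at 10% missing per arm, effect 48 m.** Zeros: difference 43.2 m, standard error 20.6 m, power about 55%. Observed cases (108 per arm): standard error 12.6 m, power about 97%.

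**Unequal missingness, no true effect, 15% ExLE v 25% Ex.** Difference: 0.85 × 400 − 0.75 × 400 = 40 m. Change variances 29,904 and 40,080, standard error 24.1 m, ratio 1.66. Rejection in about 38% of trials (37–39% in simulations).

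**Unequal missingness, true effect 48 m, 25% ExLE v 15% Ex.** 0.75 × 448 − 0.85 × 400 = 336 − 340 = −4 m. The benefit disappears.

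**Range.** A 10-point imbalance shifts the difference by 0.10 × μ/σ in SD units. Over means of 350–450 m and SDs of 120–160 m this is 35/160 = 0.22 to 45/120 = 0.375 SD.

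**Opposite direction on A1c** (assumed mean 7.5, SD 1.5, no true effect, 25% ExLE v 15% Ex): 0.75 × 7.5 − 0.85 × 7.5 = −0.75. The arm with more dropout looks better, and the difference is significant in about 45% of trials.

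**Equal missingness, no true effect.** Simulated rejection stays at about 5%.

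**The case against.** The best defence is that 0 was meant as zero change. The abstract describes the primary outcomes as changes, and item 20c does not say which quantity the 0 replaces. Under the same assumptions, with a control-arm change c of 0–50 m, the harm is then much smaller:

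- Equal 20% missing: the difference is 0.8 × 48 = 38.4 m and power is 92–94%.
- No true effect, 15% v 25% missing: the false difference is 0.1c, at most 5 m, with 5–7% rejection.
- 25% v 15% missing: the estimate is 0.75(48 + c) − 0.85c = 36 − 0.1c, so 31–36 m.

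What would remain is about 20% dilution and a standard error that treats imputed values as observed. But the text does not say zero change, the outcomes section describes measured values, and the planned ANOVA compares baseline with post-intervention data. The rule as written applies to raw values.

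Other limits stand. The document gives no basis for 15% v 25%; that imbalance is an illustration. Zero is a possible value for pNN50 and for morbidity counts. A reader might infer that participants who take no diabetes drug will be scored as non-adherent, or that those lost to follow-up will be counted as free of morbidity. The document does not say that a score that does not apply, or a morbidity report not received, counts as missing data. HRV exclusions are similar: they are set by design and not clearly meant for imputation. These are gaps that the rule leaves open, not stated scoring.

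**Conclusion.** The rule is wrong as written and should be replaced before any analysis by arm. It covers both primary outcomes and can hide a real benefit or create an apparent one.

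Two stronger readings are not supported. The rule does not by itself produce false positives: with equal missingness the type I error stays near 5%, and a false effect needs unequal dropout. Nor will one in five of all analysed values be artificial: the 20% applies at most to post-baseline values.

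The direction of the harm follows from the protocol's own scale definitions. Its size (power about 33% against 95%; a 40 m false difference with about 38% rejection; 0.22–0.375 SD per 10 points of imbalance) rests on assumed ISWT means, SDs and correlation, on raw-scale zeros, and on values missing completely at random.

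**What to change.** Delete the zero-imputation rule. State that all randomised participants are analysed in their assigned arm with a method valid under missing at random: either a likelihood-based mixed model on all observed values or multiple imputation. Add one sensitivity analysis for data missing not at random, for example delta-adjusted multiple imputation. State that medication-adherence scores that do not apply, HRV values excluded by design and morbidity reports not received are not set to 0. If zero change was intended, it should still be replaced, since it is a single imputation that dilutes the effect.

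The cost is revised wording, a little more analysis work and a protocol revision reported to the ethics committee. No new data are needed.

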#### Plans to give access to the full protocol, participant-level data, and statistical code {31c}

The study plan is accessible to the public through the ClinicalTrials.gov register (NCT03914924). The data supporting the findings of this study will be available from the corresponding author upon reasonable request.

## Oversight and monitoring

### Composition of the coordinating center and trial steering committee {5d}

This study will be overseen by a principal investigator who will be responsible for supervising the research center coordinators and all trial-related activities. The principal investigator will ensure that trial objectives and targets are met according to the established study schedule and protocol, as well as allocate financial resources to the trial development. Research center coordinators, in turn, will be responsible for creating a schedule for recruitment, assessments, and interventions. They will also supervise all research team members’ activities, including the assessment and intervention teams. This trial does not have a trial steering committee with independent members, nor does it include stakeholder or public involvement groups.

### Composition of the data monitoring committee, its role, and reporting structure {21a}

The present study does not establish a data and safety monitoring board, as both the exercise and the education interventions are considered low-risk interventions with no substantial safety issues.

### Adverse event reporting and harms {22}

Due to the low-risk nature of the trial, no adverse event is anticipated. Any unintended effects of exercise intervention will be reported to the Research Ethics Committees at the Federal University of Juiz de Fora or the Federal University of Minas Gerais.

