## Abstract

**Background:**

Patient education is a crucial strategy for promoting prevention and diabetes self-management since glycemic control achievement involves taking medications, medical nutrition therapy, physical exercise, and behavior changes. However, patient education programs are still barely implemented in low- and middle-income countries. This trial aims to investigate whether a lifestyle education intervention added to physical exercising is superior to sole physical exercising regarding functional capacity, disease-related knowledge, health behaviors, cardiometabolic health parameters, quality of life, depression, and diet quality in individuals with prediabetes or diabetes.

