### Exercise Program

The Ex program was developed based on recommendations of the Brazilian Diabetes Society Guidelines [28, 29]. It will last 12 weeks and consist of aerobic exercise sessions designed to achieve a minimum of 150 min per week, with muscle-strengthening exercises incorporated two to three times per week starting from the fourth week of the intervention. Each exercise session will include warm-up (stretching), aerobic exercise (moderate-to-vigorous intensity walking according to the Borg Rating of Perceived Exertion exercise scale modified [35]), and muscle-strengthening using the own body weight and elastic bands (one-to-two sets of 10–12 repetitions of row, half-squat or leg extension, biceps curl, standing knee flexion, shoulder external rotation, heel raise, wall push up, lying down abdominal, elbow extension, and 15 s of plank).

For participants receiving the intervention on-site, 16 supervised 1-h exercise sessions will be delivered twice a week from the first 4 weeks and once a week from the fifth week onward. In addition, these participants will receive counseling to exercise in the community to accumulate 150 min per week of aerobic exercise and perform muscle-strengthening exercises 2 to 3 times per week.

Participants receiving the intervention remotely will first attend an on-site supervised exercise session to be instructed on the correct execution of aerobic and strengthening exercises to ensure proper performance. After this initial session, the exercise intervention will be delivered through a website specifically developed for the Ex program participants. Additionally, participants will receive weekly reminders about the exercise routine via WhatsApp messages from the research team.

Participants will receive guidance on recognizing signs and symptoms of effort intolerance and instructions on how to respond in such situations. They will be asked to record their weekly exercise routine and any exercise side effects in an exercise diary. Additionally, they will be encouraged to self-monitor their heart rate by taking their pulse before and after exercise. Participants who use insulin or secretagogue medications will be instructed to measure capillary blood glucose before and after exercise. Participants with hypertension will be counseled to measure blood pressure before exercise during the first two sessions or in subsequent sessions if symptoms suggestive of changing blood pressure levels are present.

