### Exercise and Lifestyle Education Program

The ExLE program combines the Ex program with a patient education program tailored for Brazilians living with diabetes and prediabetes, with detailed descriptions available in a previously published study [25]. The ExLE will last 12 weeks and consist of the same procedures described for the Ex program plus eighteen education classes following the schedule of educational sessions for the Diabetes College program in Brazil [25].

For participants receiving the intervention on-site, 18 30-min education classes will be delivered twice a week during the first 4 weeks and once a week from the 5th week onward, before or after the supervised 1-h exercise sessions. Participants will receive a printed version of the Diabetes College patient guide [36].

Participants receiving the intervention remotely will first attend an on-site supervised exercise session to be instructed on aerobic and strengthening exercises exertion and ensure proper exercise execution. Additionally, they will receive orientation on navigating the ExLE program website to access and fill out exercise and study diaries, as well as access educational video lessons and other support materials. After this on-site session, both the exercise and patient education components of the program will be delivered through a website specific to ExLE program participants developed for this study.

The educational content will include:Eighteen educational video lessons: recorded by the research team, lasting approximately 20 min each, and based on the Diabetes College program in Brazil;Twelve videos related to weekly topics: THRiVE videos integrating chronic disease management and behavior change principles to help develop self-management skills through goal setting and action planning; and, A printed version of the Diabetes College patient guide [36].

Additionally, participants will receive weekly WhatsApp text messages from the research team to remind them about the exercise routine, materials in their lesson plan, and the importance of tracking access to educational content in the study diary.

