### Strategies to improve adherence to interventions {11c}

In on-site delivery mode, participants who did not attend the intervention session for that week will receive a WhatsApp message from the research team to remind them of the scheduled intervention for the following week. In remote delivery mode, the research team will check participants’ exercise and/or study diary completion to assess their engagement in exercise and/or education lessons. Participants who show no engagement in exercise and/or educational lessons for that week will receive a WhatsApp message reminding them about the exercise and/or study routine.

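### Adverse event reporting covers only effects of the exercise, which both arms share, so effects of the education and other non-exercise events in the 12 weeks or at assessment visits have no stated reporting route

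*Protocol article*

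**What the plan says.** The Abstract states the trial's question as "whether a lifestyle education intervention added to physical exercising is superior to sole physical exercising". The section on the Exercise and Lifestyle Education Program builds that arm on the other one: it will "consist of the same procedures described for the Ex program plus eighteen education classes".

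Adverse event reporting and harms {22} has two sentences. The first sets the expectation: "Due to the low-risk nature of the trial, no adverse event is anticipated". The second sets the rule: "Any unintended effects of exercise intervention will be reported to the Research Ethics Committees" at the two universities.

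For the intervention period, the Exercise Program section gives the means of capture, which applies to both arms: "They will be asked to record their weekly exercise routine and any exercise side effects in an exercise diary".

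One tertiary outcome is not tied to exercise. Diabetes-related morbidity is the "number and description of acute complications and diagnoses of chronic complications of diabetes, along with the number of hospitalizations associated with diabetes". It is collected by a three-item tool in the 6-month follow-up and compared between arms with a t-test.

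**The concern.** The reporting rule is keyed to the component that does not differ between arms. The added component is education, which is meant to change behaviour. The behaviours measured include diet, physical activity and medication adherence. An unintended consequence of such a change need not look like an effect of exercise, and the rule as worded would then leave it out.

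The rule also applies an attribution filter before anything is counted. The diary asks participants for side effects of exercise, so they make the first judgement of cause, and Who will be blinded {17a} says they know their arm. A comparison of harms is easier to interpret when all events are recorded first and attribution is added as a separate item.

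What is at stake is the benefit–harm statement. The Abstract's Discussion says that a favourable result could support broad delivery in Brazilian primary care. A harms record limited to exercise is a thin basis for saying that adding education did no harm.

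**Working it through.** No arithmetic on sample size, power or event rates applies. The check sets the sections on interventions, outcomes and harms side by side.

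**Step 1: what differs between arms.** The combined programme contains all the exercise procedures of the comparator plus eighteen education classes. Exercise is common to both arms; education is the contrast.

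**Step 2: which events have a stated route.**

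| Event | Stated capture | Stated route |
|---|---|---|
| Exercise side effect in the 12 weeks | Diary, both arms | Ethics committees |
| Unintended effect of education in the 12 weeks | None | None |
| Other event not attributed to exercise in the 12 weeks | None | None |
| Non-exercise-programme event at an assessment visit, such as during the shuttle walk test | None | None |
| Diabetes-related complication or hospitalisation in follow-up | Morbidity tool | Tertiary outcome, compared by arm |

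The shuttle walk test belongs in the fourth row because it is an outcome measure and not part of the exercise programme. Composition of the data monitoring committee {21a} names both exercise and education as interventions, but the harms section carries only exercise forward.

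**Step 3: how far the morbidity tool helps.** The trial lasts 9 months, of which the tool covers the 6-month follow-up. That leaves 9 − 6 = 3 months (the 12-week intervention), or 3/9 = one third of the trial. Education is delivered in that third. Within the months it does cover, the tool takes only diabetes-related events.

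**Step 4: whether the sections agree on expected harm.** The harms section anticipates no adverse event. Frequency and plans for auditing trial conduct {23} speaks of a low risk of such events, which is not the same as none. The Exercise Program section sets out precautions: guidance on effort intolerance, side-effect recording, and glucose and blood pressure checks for certain participants. These statements need to be reconciled.

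**Step 5: what can still be changed.** Trial status gives the end of recruitment as February 2024, the protocol version date as 26 June 2024, and the expected end of data collection as December 2024. If every participant is to complete 6 months of follow-up by December 2024, the last intervention must have ended by about June 2024. Prospective capture during the intervention was therefore over, or nearly so, when this version was dated. The remaining monthly calls and final visits were still ahead.

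**The case against.** The strongest reply is that the quoted sentence governs what goes to the ethics committees and does not define everything that is collected or published. That is correct, and it limits the point. A reader might infer that the harms record cannot show any harm added by education, but the documents do not support that:

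- Diabetes-related morbidity is collected whatever its cause and compared between arms. Harm acting through diet or medication-taking is much of what it would detect, though only in follow-up.
- Depression, quality of life and A1c are also compared between groups.
- Both arms keep the exercise diary. If education changes how much people exercise, exercise side effects could differ by arm, and that difference would itself be an effect of adding education.

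A second tempting inference is that nobody reads the diary's side-effect entries, because Strategies to improve adherence {11c} describes a check of "study diary completion to assess their engagement in exercise and/or education lessons". That section is about adherence. It does not say the entries go unread, and role-specific manuals are mentioned elsewhere. Who reads a diary field, or what a reminder message asks, is detail that an article commonly leaves out.

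A third is to size the gap by counting walk tests: 3 assessments × 240 participants = 720 at most. That counts tests, not events. Up to 240 of them are baseline tests done before allocation is released, so they cannot show harm added by either arm.

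It can also be said that precautions are not predictions, so the Exercise Program section does not strictly contradict the expectation of no events. That is fair. The wording is loose and needs reconciling, but it is not a flat contradiction.

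None of this supplies a route for a non-exercise event in the 12 weeks or at an assessment visit. The protocol states a scope, and that scope is too narrow for the trial's question. This is not a detail lost in condensing.

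**Conclusion.** The point holds in a limited form. The stated adverse event rule reaches only effects attributed to exercise. Unintended effects of education, and any other event not attributed to exercise during the 12-week intervention or at assessment visits, have no stated reporting route. The morbidity outcome offsets this only in part, because it is confined to diabetes-related events in follow-up.

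The gap covers the added component and about one third of each participant's time in the trial. Its size in events is unknown, since the protocol gives no rates, and it may be small in a trial considered low-risk. The primary analysis is not affected. The conclusion assumes that no wider rule for collecting adverse events exists in the full protocol or manuals; if one does, the published harms section should state it.

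**What to change.** Reword Adverse event reporting and harms {22} so that adverse events are recorded and reported in both arms whatever the suspected cause, by the same method and including events at assessment visits. Then:

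- Extract the side-effect entries from the exercise diaries of both arms.
- Ask one open all-cause question at the remaining monthly calls and final visits, including recall of the intervention period.
- Tabulate events by arm and delivery mode, with attribution in a separate column. Delivery mode matters because remote participants have one supervised session and on-site participants 16, so remote capture depends more on the diary.
- State in the report that all-cause events were not captured prospectively for intervention periods already finished.
- Reconcile the expectation of no adverse events with the low risk stated under {23} and with the precautions in the Exercise Program section.

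The cost is a change of wording, diary extraction, one question at contacts already planned, and one table. The downside is that more minor unrelated events will be recorded. Events from the intervention period that are not in the diaries will rest on recall, which is weaker than prospective capture and may differ between arms because participants know their allocation.
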